# Combining Intensive Rehabilitation With a Nonfunctional Isokinetic Strengthening Program in Adolescents With Cerebral Palsy: Protocol for a Randomized Controlled Trial

**DOI:** 10.2196/43221

**Published:** 2023-05-03

**Keywords:** isokinetic, cerebral palsy, gait analysis, spasticity, muscle strength

## Abstract

**Background:**

Cerebral palsy is the most common brain injury in the pediatric population. Patients with cerebral palsy present different affectations such as decreased muscle strength, gait deviations, impaired proprioception, and spasticity. Isokinetic strengthening programs combined with intensive rehabilitation may improve muscle strength and therefore gait efficiency.

**Objective:**

The primary aim of this randomized controlled trial is to compare the effect of an intensive rehabilitation combined with a nonfunctional isokinetic progressive strengthening program to an intensive rehabilitation alone on gait parameters and muscle strength in patients with cerebral palsy. Another goal of this study is to determine whether adding an isokinetic program to intensive rehabilitation is more effective than intensive rehabilitation alone at decreasing spasticity and improving joint position sense in patients with cerebral palsy.

**Methods:**

A total of 30 adolescents with spastic diplegia cerebral palsy (Gross Motor Function Classification System levels I to III) will be randomized, by an independent researcher, into a 3-week intensive rehabilitation and isokinetic progressive strengthening group or an intensive rehabilitation control group. Gait parameters, muscle strength, spasticity, and knee joint position sense will be assessed. These variables will be evaluated at baseline (T0) and at the end of the intervention (T1). The intensive rehabilitation will consist of physiotherapy sessions twice a day and hydrotherapy and virtual reality gait training once a day. The isokinetic training group will have a total of 9 supervised isokinetic strength training sessions focusing on knee flexors and extensors with different execution speeds.

**Results:**

The protocol has been accepted by the French National Ethics Committee in October 2022. The inclusion of patients will start in November 2022.

**Conclusions:**

The combination of intensive rehabilitation with an isokinetic program on knee flexors and extensors has not been studied yet. The findings of this study may determine if an isokinetic strength training program of knee flexors and extensors is beneficial for the improvement of gait parameters, muscle strength, spasticity, and joint position sense in adolescents with spastic diplegia.

**International Registered Report Identifier (IRRID):**

PRR1-10.2196/43221

## Introduction

### Background

Cerebral palsy is considered the most common brain injury in the pediatric population [1]. Motor impairments are commonly observed in adolescents with cerebral palsy [2]. Sensory impairments, cognitive disorders, epilepsy, and nutritional deficiencies are also often found in patients with cerebral palsy [2]. Cerebral palsy prevalence ranges from 1.5 to 2.5 cases per 1000 births and does not differ within different western countries [3]. Spasticity is regularly described as the most common motor impairment in the cerebral palsy population and is characterized by an increased stretch reflex. Spasticity is movement dependent, increasing with a higher velocity [4]. Spasticity is often measured through an isokinetic dynamometer to passively stretch the targeted muscles [4-6].

Muscle strength is commonly decreased in adolescents with cerebral palsy. Quadriceps and hamstring muscles are important to perform daily activities such as standing, walking, and climbing stairs [7]. Knee extensor strength is described as a good indicator of total lower limb muscle strength. Isokinetic dynamometry is the gold standard to measure muscle strength [6]. Isokinetic dynamometry has been described as a reliable tool to measure quadriceps and hamstring muscle strength in children with cerebral palsy [6]. Isokinetic dynamometry can also be used within a reeducation program to increase muscle strength in children with cerebral palsy [6]. An isokinetic strength training program focusing on knee flexors and extensors has shown some promising results in improving muscle strength in children with cerebral palsy [8]. MacPhail and Kramer [8] did not find any improvement in gait parameters in patients with cerebral palsy after an isokinetic program focusing on knee flexors and extensors. However, they did not implement such a program within an intensive rehabilitation program. A recent systematic review has shown that an isokinetic strength training program focusing on knee flexors and extensors improves muscle strength, mobility, and gait in patients with stroke [9]. Functional power training has been shown to be effective training to improve muscle strength, walking capacities, and resting somatosensory cortical activity in children with cerebral palsy [10-12]. Power training exercises such as walking, sit-to-stand, and side-walking should form part of an intensive rehabilitation program. Medium-speed concentric and eccentric isokinetic training is considered strength training, whereas low-speed isokinetic training produces hypertrophy [13]. Finally, high-speed isokinetic training is described as power training [13].

Gait deviations are frequently observed in adolescents with cerebral palsy due to motor impairment. Gait speed, stride length, step width, and stance time are important factors for an effective gait [14,15]. Lower limb muscle fatigue is commonly observed in patients with cerebral palsy and drastically affects their gait abilities and distances [16,17]. Usually, patients with cerebral palsy receive physiotherapy treatment for long periods; however, decreased muscle strength of the lower limbs has been shown to be associated with impaired gait function in children with cerebral palsy. Therefore, treatment for patients with cerebral palsy should focus on strengthening lower limb muscles to improve gait parameters [15,18].

Proprioception has been defined as the ability of an individual to integrate sensory signals from mechanoreceptors, allowing him to determine the position of a joint in space and its movement [19]. Knee proprioception is provided by afferent signals that are located inside or around the joint [19,20]. Its functions are to protect the knee joint against excessive injurious movement, stabilize the knee during static postures, and coordinate complex movements [19-21]. Wingert et al [22] have shown that children with cerebral palsy who present with gait disturbances have poorer proprioception than typically developing children. Over the last decade, 2 different proprioception assessment techniques have been described in the literature [21]: joint position sense and joint motion sense. Strength training has been described as an effective intervention to improve proprioception in children with cerebral palsy [23].

Intensive rehabilitation has been shown to be an effective program to improve functional motor outcomes in children with cerebral palsy [7,24-26]. A recent practice guideline to improve physical function in children with cerebral palsy has shown that a high enough dose of practice is required in order to improve motor abilities [26]. Jackman et al [26] have shown that intensive blocks of therapy were better than low-dose regular therapy in order to improve motor abilities in patients with cerebral palsy. Elgawish and Zakaria [27] have shown that intensive physiotherapy is more effective than standard physiotherapy in improving gross motor function in children with spastic diplegia. Bleyenheuft et al [24,25] have shown that an intensive training protocol including upper and lower extremities was effective in improving lower extremity function in children with unilateral and bilateral spastic cerebral palsy. In a meta-analysis, Moreau et al [28] have shown that gait training is an important component of rehabilitation to improve gait parameters, such as gait speed, in children with cerebral palsy. In their clinical guideline, Jackman et al [26] have shown that 30 to 40 hours of practice are required to improve motor abilities. Combining intensive rehabilitation with an isokinetic strengthening program has not been studied yet.

### Objectives

The primary aim of this randomized controlled trial is to compare the effect of intensive rehabilitation combined with an isokinetic progressive strengthening program to intensive rehabilitation alone on gait parameters and muscle strength in patients with cerebral palsy. Another goal of this study is to determine whether adding an isokinetic program is more effective than just intensive rehabilitation in decreasing spasticity and improving joint position sense in patients with cerebral palsy.

## Methods

### Study Design

This study will be a prospective randomized controlled trial. Adolescents with spastic diplegia cerebral palsy will be randomized by an independent researcher through a computer-based method into an isokinetic training group (IG) or a control group (CG). The block randomization method will be used to keep the number of subjects in each group equal. The IG will receive a 3-week isokinetic strengthening program together with intensive rehabilitation, and the CG will only follow the intensive rehabilitation. Patients will not be informed if they are part of the intervention or the CG. Outcome measures will be done at baseline (T0) and at the end of the intervention (T1). The protocol has been accepted by the French National Ethics Committee (IDRCB: 2022-A00431-42).

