### Sample Size

Sample size calculation was realized using G*POWER statistical programming (version 3.1.9.2; Franz Faul): power (1−α error *P*)=.85, α=.05, effect size=1.1, with a 2-tailed for a comparison of 2 independent groups. This calculation was based on the results of a pilot study based on ratio improvement following 2 specific interventions in patients with cerebral palsy. It will take 15 participants in each group to complete this study.

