### Participants

A total of 30 pediatric patients will be recruited from the Institut St Pierre, France. The inclusion criteria for this study will be adolescents aged from 11 up to 18 years with a diagnosed spastic diplegia cerebral palsy, patients with walking abilities (Gross Motor Function Classification System levels I to III), the ability to activate knee flexors and extensors voluntarily, and cognitive abilities to understand the instructions. The exclusion criteria for this study will be cardiovascular disorders; fractures of any type; history of hip subluxation, dislocation, or important scoliosis (>40° of curvature); surgery of the lower limb within the last year; botulinum toxin injection within the last 3 months; significant contracture of the knee flexors and extensors (less than 90° of knee active range of motion [ROM]); and insufficient understanding of the French language. All the participants and their legal tutor will be informed of the study procedures in agreement with the ethical standards of the Helsinki Declaration and will sign an informed consent.

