### Data Analysis

Descriptive statistics will be used to describe gender, age, and Gross Motor Function Classification System. Primary and secondary outcomes will be analyzed in the same way. The assumption of normality will be checked by visual inspection of the q-q plot and the box plot of the data within groups. A Shapiro-Wilks test will also be performed on the data within groups. The homogeneity of variance will be checked using Levene test.

If the data are normally distributed, an independent *t* test will be carried out for each variable to see if there are differences between the experimental and control groups. The 95% CI for the mean differences will be determined. Pearson *r* will be used to calculate the effect size.

If the data are not normally distributed, a Wilcoxon rank-sum test will be used for each variable to determine if there are any significant differences between groups. Pearson *r* will be calculated as a measure of effect size.

The data analysis will be performed using SPSS (25.00, IBM Corp). For the data analysis, the researchers will use a 95% CI, considering all those variables with a *P* value of less than .05 to be statistically significant.

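### The unadjusted group comparison leaves GMFCS level and baseline values unused, which gives up precision and leaves a 30-patient estimate exposed to chance imbalance

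*Protocol article*

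**What the plan says.** Eligibility (Participants) covers "patients with walking abilities (Gross Motor Function Classification System levels I to III", with no quota or expected number per level. The same section gives the total: "A total of 30 pediatric patients will be recruited from the Institut St Pierre, France".

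Study Design describes a computer-generated blocked allocation and gives one purpose for the blocks: "The block randomization method will be used to keep the number of subjects in each group equal". No stratification factor is named. Outcomes are measured at T0 and T1.

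Data Analysis gives GMFCS one role: "Descriptive statistics will be used to describe gender, age, and Gross Motor Function Classification System". The comparison for every primary and secondary outcome is an independent t test, or a Wilcoxon rank-sum test if the data are not normal. Neither has a covariate. The section does not say whether T1 values or changes from T0 are compared.

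Sample Size assumes "α=.05, effect size=1.1, with a 2-tailed for a comparison of 2 independent groups" at 85% power and concludes "It will take 15 participants in each group to complete this study". The effect size is "based on the results of a pilot study based on ratio improvement following 2 specific interventions".

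**The concern.** GMFCS is the only motor-severity classification in the eligibility criteria. It is known before allocation, and it grades the kind of function that several primary outcomes also measure: gait speed, 6-minute walking distance and knee strength. Blocks without strata equalise head count only. In 30 patients the two groups can easily differ in their share of level III patients, and a test without covariates makes no correction for that.

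Two things are at stake. Variance that the collected baseline data could explain stays in the error term. And the estimate from the one allocation that is drawn can be pulled up or down by the mix of levels. Neither T0 nor GMFCS needs any further data collection.

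**Working it through.** **The plan's own figure.** Inputs from Sample Size: effect size d = 1.1, two-sided α = 0.05, power 0.85, two independent groups.
- Normal approximation: n = 2(1.960 + 1.036)² / 1.1² = 14.8, so 15 per group. The stated figure is reproduced.
- Exact noncentral t at 15 per group: noncentrality 1.1 × √(15/2) = 3.01, 28 df, power 0.828. This is the baseline for the comparisons below.

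**Chance of imbalance.** The GMFCS mix is not given, so assume K = 8, 10 or 12 level III patients among 30, allocated 15:15. With x level III patients in one group, P(x) = C(K, x) · C(30−K, 15−x) / C(30, 15). Sum over all x with |2x − K| ≥ 4:

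| K | P(groups differ by at least 4) |
|---|---|
| 8 | 0.215 |
| 10 | 0.245 |
| 12 | 0.264 |

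**Size of the shift.** With K = 10, a 7-3 split makes the level III shares differ by 7/15 − 3/15 = 4/15. If level III differs from I-II by Δ, the unadjusted difference moves by (4/15)Δ. Δ follows from the assumed share of variance R² explained by GMFCS, with p = 1/3 and p(1−p) = 2/9:
- in units of the total SD, Δ = √(R² / (2/9));
- in units of the SD within level, Δ = √(R² / ((1−R²) · 2/9)).

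| R² | Δ (total SD; within-level SD) | Shift = (4/15)Δ |
|---|---|---|
| 0.05 | 0.47; 0.49 | 0.13; 0.13 |
| 0.20 | 0.95; 1.06 | 0.25; 0.28 |

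The shift is therefore about 0.13 to 0.28 SD. Against the planned 1.1 that is 0.13/1.1 = 12% to 0.28/1.1 = 25%.

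**Gain from adjustment.** The residual SD becomes √(1−R²), where R² is now the share explained by the covariates in the model. Noncentrality = 1.1/√(1−R²) × √(15/2), with 27 df for one covariate and 26 df for two:

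| R² | Power, 27 df | Power, 26 df |
|---|---|---|
| 0 | 0.827 | 0.826 |
| 0.05 | 0.846 | 0.845 |
| 0.10 | 0.864 | 0.864 |
| 0.20 | 0.901 | 0.900 |

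The unadjusted test has 0.828. Covariates that explain nothing cost about 0.002 of power.

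**Type I error.** In simulation (100,000 allocations for each R², 10 patients per level, R² = 0.1, 0.3 and 0.5), the unadjusted t test rejected in 4.9% to 5.1% of trials with no effect. If allocation were perfectly balanced on GMFCS but the test left unadjusted, it would be conservative: about 3.9% at R² = 0.1.

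**The case against.** **Stratification may simply be unreported.** This is a condensed article, and the full protocol may name strata. That stands: absence of stratification is not established and is not claimed here. The test without covariates, however, is stated outright. If the full protocol does stratify by GMFCS, an unadjusted test remains the wrong partner for it, as the 3.9% above shows.

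**A reader might infer that a treatment effect could not be told apart from a different case mix.** The documents do not support that. Randomisation is valid without stratification, and the t test allows for chance imbalance on average. GMFCS will be described and every outcome is measured at T0, so an imbalance would be visible. The shift calculated above applies to an unlucky draw, not to the design as a whole.

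**A reader might also infer a larger shift.** A level III difference of 1.5 SD would require GMFCS to explain about 33% (within-level SD) to 50% (total SD) of outcome variance. Nothing in the article supports that, and it lies outside the 5% to 20% range used here.

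**The scale is uncertain.** The effect size rests on an improvement ratio, and Data Analysis does not say whether changes are compared. If they are, differences in starting level largely cancel, and only a link between GMFCS and response to treatment would matter. This stands, and the shift would then be smaller.

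**Most of the benefit may come from T0.** Probably so. What GMFCS adds on top of T0 is likely near the low end, roughly two points of power.

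**Conclusion.** The point holds as an improvement to the analysis, not as a flaw in validity. The plan commits to unadjusted tests while holding baseline information that costs nothing to use.

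Its size is modest: a 21% to 26% chance of a level III difference of at least 4, a shift of about 0.13 to 0.28 SD in a 7-3 split, and power of about 0.85 to 0.90 instead of 0.83. These figures rest on three assumptions that the documents neither give nor contradict: 8 to 12 level III patients (10 for the shift), a covariate R² of 0.05 to 0.20, and an effect of 1.1 SD on the scale analysed. With an R² of 0.10, adjustment takes exact power above the planned 0.85 without extra patients.

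**What to change.** In Data Analysis, replace the unadjusted comparison by an ANCOVA of the T1 value on group, with the T0 value of the same outcome and GMFCS (I-II versus III) as covariates. Report the adjusted difference with its 95% CI. Specify this before any data are compared by group. It also settles whether T1 values or changes are analysed. The normality check then applies to the residuals, and if the rank-based fallback is kept it needs a covariate-adjusted counterpart.

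Stratification is optional. If the full protocol does not already stratify and the list is not yet in use, it may be generated in the same two GMFCS strata. Inclusion was due to start in November 2022 and the article appeared in May 2023, so this is probably too late. A list already in use should be kept. The covariate is the essential change.

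Cost: a few lines of wording and one degree of freedom per covariate. The two-level grouping leaves an imbalance between levels I and II to be handled through T0. If strata are used, group sizes may differ by an unfinished block.

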### Sample Size

Sample size calculation was realized using G*POWER statistical programming (version 3.1.9.2; Franz Faul): power (1−α error *P*)=.85, α=.05, effect size=1.1, with a 2-tailed for a comparison of 2 independent groups. This calculation was based on the results of a pilot study based on ratio improvement following 2 specific interventions in patients with cerebral palsy. It will take 15 participants in each group to complete this study.

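### At the printed effect size of 1.1, 15 per group gives exact power of about 0.83 rather than .85, and recruiting exactly 30 means one missing T1 assessment loses the stated .85 on any reading

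*Protocol article*

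**What the plan says.** The Sample Size section names its software ("Sample size calculation was realized using G*POWER statistical programming (version 3.1.9.2; Franz Faul") and its inputs: a target power of .85, printed with the label 1−α, together with "α=.05, effect size=1.1, with a 2-tailed for a comparison of 2 independent groups". The effect size comes from a pilot study. The result is given as "It will take 15 participants in each group to complete this study".

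The Participants section sets recruitment at the same figure: "A total of 30 pediatric patients will be recruited from the Institut St Pierre, France". The Study Design section uses block randomization to keep the groups equal and measures outcomes at T0 and T1 only. The Data Analysis section compares the groups by independent t test when the data are normally distributed. The Ethics Approval section lets participants leave the study whenever they wish. No rate of loss and no allowance for loss is stated.

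**The concern.** Two things do not fit.

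1. G*Power's test for two independent means uses the noncentral t distribution. With the printed inputs that calculation returns 16 per group, not 15.
2. The number recruited, 30, equals twice the 15 per group that the calculation requires. The stated power therefore presupposes that every randomized adolescent supplies a T1 assessment, in a trial that permits withdrawal.

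At stake is a published design property. If the trial ends without a significant difference, readers will judge that result against a power of .85, which the printed inputs do not give for the planned test and which no reading of them gives after one loss.

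**Working it through.** **Inputs.** Two-sided alpha .05, target power .85, effect size 1.1 read as Cohen's d (the type is not named), and 15 per group, all from Sample Size. Equal allocation is from Study Design, the independent t test from Data Analysis, and 30 recruited from Participants.

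**Step 1: reproduce the plan's figure.** The normal approximation is n per group = 2(z₀.₉₇₅ + z₀.₈₅)² / d².

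2 × (1.960 + 1.036)² / 1.1² = 14.84, rounded up to 15. By the same approximation, power at 15 per group is Φ(1.1 × √7.5 − 1.960) = 0.854. So 15 is reproduced this way.

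**Step 2: the planned test.** The t test estimates the SD, so its power comes from the noncentral t with df = n₁ + n₂ − 2 and noncentrality δ = d√[n₁n₂/(n₁+n₂)]:

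- 15/15: δ = 1.1 × √7.5 = 3.013, df = 28, critical t = 2.048, power = 0.828.
- 16/16: δ = 1.1 × √8 = 3.111, df = 30, critical t = 2.042, power = 0.853.

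The shortfall at 15 per group is 0.850 − 0.828 = 0.022. A one-sided test at 15 per group would have power 0.902, so sidedness does not explain the figure.

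**Step 3: rounding of the effect size.** Exact power at 15/15 for values near 1.1:

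| d | Power at 15/15 | n per group for .85 |
|---|---|---|
| 1.05 | 0.793 | 18 |
| 1.10 | 0.828 | 16 |
| 1.13 | 0.848 | 16 |
| 1.134 | 0.850 | 15 |
| 1.149 | 0.859 | 15 |

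An effect size from about 1.134 to 1.149 prints as 1.1 and gives 15. The values that print as 1.1 run from 1.05 to just under 1.15, so this is roughly the top sixth of the range: (1.15 − 1.134)/0.10 = 0.16.

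**Step 4: losses.** The documents state no rate, so these are scenarios. Exact t test, with participants lacking T1 left out of the comparison:

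| Evaluable | Power, d = 1.1 |
|---|---|
| 15/15 | 0.828 |
| 15/14 | 0.814 |
| 14/14 | 0.800 |
| 13/15 | 0.798 |
| 13/13 | 0.768 |

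At d = 1.149, close to the largest value that still prints as 1.1, 15/14 gives δ = 1.149 × √(210/29) = 3.092 and power 0.846. The normal approximation at d = 1.1 with 15/14 gives Φ(2.960 − 1.960) = Φ(1.000) = 0.841. Each reading that returns 15 per group therefore falls below .85 after one loss.

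**The case against.** The strongest reply is that the effect size is printed to one decimal. Users of G*Power often enter an unrounded value computed from pilot means and SDs, and this figure is said to come from a pilot study. If the input was, say, 1.14, then 15 per group has power 0.854 and the calculation is correct. The normal approximation also returns 15, and the difference is one participant per group and 2.2 power points. This reply stands to a degree. A reader might infer that the design fails to reach .85 even with perfect retention. The documents do not support that certainty, because the unrounded value is not given. They do show that 1.1 as printed is too coarse to support .85 with 15 per group.

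On losses, the programme lasts only three weeks, no dropout rate is given, and one loss costs about 1.4 points at d = 1.1 (0.828 to 0.814). The phrase about completing the study may also mean no more than carrying it out. All of this limits the size of the point but does not remove it: the calculation needs 15 analysed per group, and only 15 per group are recruited.

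Two further readings should be resisted:

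- That a baseline-adjusted analysis would recover the shortfall without extra enrolment. This depends on the T0–T1 correlation, which the documents do not give.
- That the rank-sum fallback has a definite lower power. A figure worked out under normality does not describe a branch used only when the data are not normal.

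**Conclusion.** The point holds in a limited form. Taking the printed inputs at face value, 15 evaluable participants per group give power of about 0.83, and 16 per group would be needed for .85. Whether the original calculation was wrong cannot be settled, since an effect size of about 1.134 to 1.149, or a normal approximation, would return 15.

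The retention part does not depend on that question. Recruitment equals the number required, withdrawal is permitted, and a single missing T1 assessment puts power below .85 on every reading examined: 0.814 at d = 1.1, 0.846 at d = 1.149.

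This rests on reading the effect size as Cohen's d and on leaving participants without T1 out of the t test. How many losses will occur is unknown. The effect on the trial is small, but the stated power is a figure readers will rely on and it is easily corrected.

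**What to change.** Either:

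- state that with 15 evaluable participants per group the power is about 0.83 for d = 1.1 (two-sided alpha .05, independent t test), falling to about 0.80 with one loss per group; or
- if the input was not exactly 1.1, give the unrounded effect size and the power at that value, with and without losses.

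The second option is the right one if the authors' input lay near 1.14, because 0.83 would then be wrong. In passing, change the power label from 1−α to 1−β; the intended meaning is clear, so this is clerical.

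The cost is wording only. The stated power becomes slightly less favourable.
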